**Study and design:**

This is a multicenter, observational, retrospective registry to be conducted at 17 centers in Spain and Italy (ClinicalTrials.gov number: NCT04359927). Consecutive patients older than 18 years, who underwent a real-time reverse transcriptase-polymerase chain reaction (RT-PCR) for SARS-CoV2 in the participating institutions, will be included since March 2020, to August 2020. Patients will be classified into two groups, according to the results of the RT-PCR: COVID-19 positive or negative. The primary outcome will be cardiovascular mortality at 1 year. The secondary outcomes will be acute myocardial infarction, stroke, heart failure hospitalization, pulmonary embolism, and serious cardiac arrhythmias, at 1 year. Outcomes will be compared between the two groups. Events will be adjudicated by an independent clinical event committee.

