Demographic data • Age • Sex Risk factors and baseline comorbidities • Hypertension • Diabetes mellitus • Hypercholesterolemia • Smoking status • Kidney chronic disease • Previous ACS • Previous Stroke • Heart failure • Atrial fibrillation • Previous PE and DVT • Cancer • Organ transplant • Immunosupresion • Frailty Charlson Comorbidity Index Baseline medication • Anti-hypertensive drugs and cardiovascular medication • Chronic anticoagulation • Oral hypoglycemic agents • Insulin • Proton pump inhibitors • NSAIDs	Symptoms Hospitalization • Length of stay Drugs: • Anti-hypertensive drugs and cardiovascular medication. • Anticoagulation • Antivirals • Immunosuppressive drugs • Vasopressors • ICU admission • Invasive mechanical ventilation Biomarkers • Hemoglobin* • Lymphocytes* • Platelets* • Creatinine** • HscTnI** • NT-proBNP** • D-dimer** • Fibrinogen* • Prothrombin time** In-hospital events: • All-cause death • Cardiovascular death • ACS • Stroke • DVT and PE • Cardiac arrhytmias • Bleeding • Red blood cell transfusion Discharge medication	New SARS-CoV-2 infection Vaccination against SARS-CoV-2 Outcomes • All cause death • Cardiovascular death • ACS • Stroke • Heart failure hospitalization • PE • Cardiac arrhytmias

ACS, acute coronary syndrome; DVT, deep venous thrombosis; Hs-cTnI, high sensitivity cardiac troponin I; NSAIDs, non-steroidal anti-inflammatory drugs; PE, pulmonary embolism.

*Lowest values during hospitalization.

*Highest values during hospitalization.

All the data will be obtained from electronic records (medical history). If deemed necessary, the investigator may check the patient vital status in the social national security database.

Clinical follow-up will be performed at 1-year. The flowchart and study timeline are detailed in **Fig 1**.

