### Outcomes and definitions

The primary outcome will be:

Cardiovascular mortality at 1-year follow-up, defined according to the Academic Research Consortium-2 [15].

The secondary outcomes will be:

Myocardial infarction: defined according to the Academic Research Consortium-2 [15].Stroke: defined according to the Academic Research Consortium-2 [15].Heart failure hospitalization must be documented in the diagnosis of the hospitalization discharge letter.Pulmonary embolism must be documented with a computed tomography.Cardiac arrhythmias must be documented in the diagnosis of the hospitalization discharge letter. Serious cardiac arrhythmias were defined as: bradycardia requiring intravenous medication or pacemaker, supraventricular tachycardia requiring intravenous medication or cardioversion, or ventricular tachycardia requiring intravenous medication or cardioversion.Major bleeding was defined as a type 3 of the Bleeding Academic Research Consortium (BARC) or higher [16].

All the events will be independently adjudicated by a Clinical Events Committee. The Clinical Event Committee (CEC) consists of cardiologists not participating in the trial. The CEC members will be blinded to PCR COVID of the patient.

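### All-cause death is collected to 1 year but missing from the outcome lists, so the only prespecified mortality outcome depends on assigned cause, and non-cardiovascular death has no stated handling

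*Protocol article*

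**What the plan says.** All of this is in the protocol article.

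- **Data capture, Table 2.** The acute-phase column has "In-hospital events: • All-cause death • Cardiovascular death". The 1-year column has "Outcomes • All cause death • Cardiovascular death".
- **Outcomes and definitions.** The primary outcome is "Cardiovascular mortality at 1-year follow-up", under a cited consensus definition. The secondary list runs from myocardial infarction to major bleeding and does not include all-cause death.
- **Abstract, Study and design.** "The secondary outcomes will be acute myocardial infarction, stroke, heart failure hospitalization, pulmonary embolism, and serious cardiac arrhythmias, at 1 year". All-cause death is absent here too.
- **Statistical analysis plan.** Event rates and curves come from Kaplan-Meier. A Cox model is named for cardiovascular death, comparing PCR-positive with PCR-negative patients. The only censoring rule concerns patients who cannot reach 1 year of follow-up.
- **Discussion.** Cox regression is said to identify predictors of mortality, without the word cardiovascular.
- **Sources of death data.** Data come from electronic records, and "If deemed necessary, the investigator may check the patient vital status in the social national security database". The Monitoring section says the blinded committee adjudicates from documents supplied by the centers.

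**The concern.** Two things follow from these statements.

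First, the article disagrees with itself on whether all-cause death is an outcome and on which mortality is modelled. If the outcome lists govern, the only prespecified mortality comparison needs a cause for every death. The optional database check is described as giving vital status, and nothing is said about cause. A death that comes to light only there may reach the committee without the papers needed to classify it. All-cause death would count it correctly whatever its cause.

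Second, death from another cause removes a patient from risk of every cardiovascular outcome. The groups are defined by an acute infection, so the frequency of non-cardiovascular death may differ between them. Without all-cause or non-cardiovascular death alongside, a reader who sees a low cardiovascular death rate in PCR-positive patients cannot tell whether few died or many died of something else first. The stated rate estimator, Kaplan-Meier, also gives too high a cardiovascular mortality if the other deaths are treated as censored.

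**Working it through.** The article states no event rate, event count or power, so there is no figure of its own to reproduce. The check is a comparison of text, followed by a bound on the Kaplan-Meier effect.

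**1. Where each kind of death appears**

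| Place in the article | All-cause death | Cardiovascular death |
|---|---|---|
| Table 2, acute phase | listed | listed |
| Table 2, 1 year, under an outcomes heading | listed | listed |
| Abstract, primary and secondary outcomes | absent | primary |
| Outcomes and definitions | absent | primary |
| Statistical analysis plan, Cox model | absent | modelled |
| Discussion, Cox model | mortality, unqualified | not specified |

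So all-cause death is collected in both phases and is in neither outcome list. Cardiovascular death is the only mortality endpoint in the lists and in the Cox sentence.

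**2. What Kaplan-Meier does if non-cardiovascular deaths are censored**

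Take one group with complete follow-up to 1 year. Let c be the true proportion dying of cardiovascular causes and q the proportion dying of other causes. Let S1 and S2 be the Kaplan-Meier survival estimates for the two causes, each censoring the other. With no tied death times, S1 × S2 = 1 − c − q, and the reported cardiovascular mortality is 1 − S1.

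- Lowest value: all cardiovascular deaths come first. Then 1 − S1 = c, which is correct.
- Highest value: all other deaths come first. Then S2 = 1 − q, S1 = (1 − c − q)/(1 − q), and 1 − S1 = c/(1 − q).

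The reported rate therefore lies between c and c/(1 − q). It is never too low, and its excess depends on q, which may differ by PCR group.

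**3. Illustration, with assumed rates**

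Assume 15% all-cause and 3% cardiovascular mortality at 1 year. Neither figure comes from the article. Then q = 15% − 3% = 12%.

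- Lowest: 3.0%.
- Causes in constant proportion over the year: 1 − 0.85^(3/15) = 3.2%.
- Highest: 3% / (1 − 0.12) = 3.4%.

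The excess is 0 to 0.4 percentage points, a factor of 1 to 1/0.88 = 1.14. With other rates, the factor 1/(1 − q) gives the upper limit.

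**4. The Cox model**

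A Cox model that censors non-cardiovascular death estimates a cause-specific hazard ratio. That is a legitimate comparison of rates among those still alive. It does not show how many patients die of cardiovascular causes by 1 year, because that also depends on the hazard of other death. This is why the companion outcome is needed; it is not a reason to abandon the model.

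**The case against.** The strongest reply has four parts.

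- **Table 2 does call all-cause death an outcome.** True. A reader might infer that it is not an outcome at all and will never be reported. The documents do not support that: it is collected under an outcomes heading, the Kaplan-Meier sentence is not limited to cardiovascular death, and the Discussion speaks of mortality in general. What stands is that the two outcome lists omit it.
- **The handling of unknown cause is not shown, rather than wrong.** A reader might infer that deaths found through the database cannot be classified and are dropped or censored. Nothing says so. The check is optional, the article does not say whether the database holds a cause, and such a patient may still have hospital records. The cited definition, the committee's charter or the full plan may set a rule for undetermined deaths. It stands only that these deaths may lack documents on cause.
- **The size cannot be taken from unknown-cause deaths.** It is tempting to apply an assumed unknown-cause share to all deaths. The article gives no such share, and the mechanism reaches only deaths known solely through the look-up. In-hospital deaths, recorded as acute-phase events, are the likeliest to have records.
- **Competing-risk detail belongs in a fuller plan, and the registry's focus is cardiovascular.** This has some force. But the article sets out its outcomes in two places and names its rate estimator, so both are choices made here.

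Nor should the secondary outcomes be read as non-fatal only; the article does not restrict them so.

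**Conclusion.** The point holds as an inconsistency with a practical consequence. The outcome lists should be reconciled with Table 2, because as they stand the only prespecified mortality outcome relies on cause assignment. The stated Kaplan-Meier method, with no word on non-cardiovascular death, would overstate cardiovascular mortality if those deaths are censored.

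The numerical size is open. The bound c/(1 − q) assumes complete follow-up and that other deaths are censored; the illustration of up to 0.4 points also rests on assumed death rates. On those rates the distortion of the cardiovascular rate is modest. The larger loss is interpretive: the group comparison cannot be read without knowing how many died of other causes. The primary outcome itself is not invalidated, and no claim is made about how many deaths will lack a cause.

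**What to change.** 1. Add all-cause death to the secondary outcomes in the abstract and in Outcomes and definitions, and compare it between PCR groups with the same Cox model as the primary.
2. Make the Statistical analysis plan and the Discussion agree on which mortality is modelled.
3. Report cardiovascular and non-cardiovascular death by group as cumulative incidence functions in place of Kaplan-Meier rates. Kaplan-Meier remains suitable for all-cause death.
4. Count any death of undetermined cause in all-cause death, and repeat the primary analysis with such deaths taken as cardiovascular and then as non-cardiovascular.

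The cost is a few extra analyses and tables, using death fields already in Table 2. One item needs confirming: whether the eCRF, which is not at hand, has a code for undetermined cause. If not, that code would have to be added.

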**Fig 1 pone.0255263.g001:**
[figure not shown]
Timeline of the study. Inclusion of the patients will be since March to August 2020. Analysis of the clinical outcomes will be performed in August 2021.

### Monitoring

Independent study monitors (Effice, Madrid, Spain) verified the adequacy of the follow-up and events reported, conducting auditing in a random sample of 10% of all patients included. All events were adjudicated and classified by an independent event adjudication committee (**S1 Table**) blinded to the treatment groups by reviewing source documents (including angiograms) provided by each center (Barcicore Lab, Barcelona, Spain).

### Outcomes and definitions

The primary outcome will be:

Cardiovascular mortality at 1-year follow-up, defined according to the Academic Research Consortium-2 [15].

The secondary outcomes will be:

Myocardial infarction: defined according to the Academic Research Consortium-2 [15].Stroke: defined according to the Academic Research Consortium-2 [15].Heart failure hospitalization must be documented in the diagnosis of the hospitalization discharge letter.Pulmonary embolism must be documented with a computed tomography.Cardiac arrhythmias must be documented in the diagnosis of the hospitalization discharge letter. Serious cardiac arrhythmias were defined as: bradycardia requiring intravenous medication or pacemaker, supraventricular tachycardia requiring intravenous medication or cardioversion, or ventricular tachycardia requiring intravenous medication or cardioversion.Major bleeding was defined as a type 3 of the Bleeding Academic Research Consortium (BARC) or higher [16].

All the events will be independently adjudicated by a Clinical Events Committee. The Clinical Event Committee (CEC) consists of cardiologists not participating in the trial. The CEC members will be blinded to PCR COVID of the patient.

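### The serious-arrhythmia definition omits ventricular fibrillation and cardiac arrest, and the discharge-letter rule does not say what counts for patients who die in hospital

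*Protocol article*

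**What the plan says.** Three parts of the protocol article bear on this outcome.

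- **Outcomes and definitions.** The source rule is "Cardiac arrhythmias must be documented in the diagnosis of the hospitalization discharge letter". The definition that follows reads "Serious cardiac arrhythmias were defined as: bradycardia requiring intravenous medication or pacemaker", then "supraventricular tachycardia requiring intravenous medication or cardioversion, or ventricular tachycardia requiring intravenous medication or cardioversion". No further rhythm is listed. The section adds that "All the events will be independently adjudicated by a Clinical Events Committee".
- **Abstract, Study and design.** The secondary outcomes end with "pulmonary embolism, and serious cardiac arrhythmias, at 1 year".
- **Data capture, Table 2.** The acute-phase column collects "In-hospital events: • All-cause death • Cardiovascular death • ACS • Stroke • DVT and PE • Cardiac arrhytmias". The long-term column again lists arrhythmias without the word serious. The text below the table takes all data from electronic records.

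The Monitoring section says that the committee works from source documents supplied by the centers. The primary outcome, cardiovascular mortality at 1 year, follows the Academic Research Consortium-2 definition and carries no discharge-letter condition.

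**The concern.** There are two gaps and one inconsistency in the same outcome.

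First, the list is closed. A ventricular fibrillation arrest ended by defibrillation is none of the three named rhythms, and neither is asystole. An event of that kind would not count as serious, while a supraventricular tachycardia given intravenous medication would.

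Second, the source rule uses *must*. A patient who dies in hospital may have no discharge letter in the ordinary sense, and the article does not say whether a death summary takes its place.

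Third, the outcome is called serious arrhythmia in the Abstract, arrhythmia in Table 2, and both in Outcomes and definitions. These names define different event counts.

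At stake is a secondary comparison between patients with positive and negative tests. Both gaps bear most on patients who die. If one group has more in-hospital deaths, it loses more events.

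**Working it through.** **No figure to reproduce.** The Statistical analysis plan section says that no precise sample size was estimated, and the article gives no event rates, deaths by group or arrhythmia frequencies. The check is therefore a reading of the text, followed by an illustration in which every input is assumed.

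**Reading of the text.**

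| Question | What the article gives |
|---|---|
| Does the list cover ventricular fibrillation, asystole, cardiac arrest or defibrillation? | None is named |
| Does any section name a source for an arrhythmia in a patient who dies in hospital? | No. Table 2 collects in-hospital deaths and arrhythmias, and the committee sees source documents, but neither statement lifts the *must* |
| Does the article say that an in-hospital death leaves no discharge letter, or that a death summary is refused? | No; it is silent |
| Does the primary outcome depend on the rule? | No |

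**Illustration: inputs, all assumed.** d = in-hospital death risk, 10% in positives and 3% in negatives. a_D = serious-arrhythmia risk in patients who die, 10% or 20%. a_S = the same in survivors, 2%. c = share of arrhythmias in patients who die that meet both the source rule and the list. Capture in survivors is set to 1, so losses of survived ventricular fibrillation are not modelled.

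**Formula for simple proportions.** Counted risk = d × a_D × c + (1 − d) × a_S.

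For a_D = 10%:
- c = 1: 0.010 + 0.018 = 2.80% against 0.003 + 0.0194 = 2.24%; ratio 1.25.
- c = 0.5: 0.005 + 0.018 = 2.30% against 0.0015 + 0.0194 = 2.09%; ratio 1.10.

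For a_D = 20%:
- c = 1: 0.020 + 0.018 = 3.80% against 0.006 + 0.0194 = 2.54%; ratio 1.50.
- c = 0.5: 0.010 + 0.018 = 2.80% against 0.003 + 0.0194 = 2.24%; ratio 1.25.

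At half capture the events lost are 18-26% in positives and 7-12% in negatives. With equal deaths (5% in both groups) the ratio is 1.00 at every value of c, and with c = 1 nothing is lost.

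**Limit at zero capture.** With c = 0 the formula gives 1.80% / 1.94% = 0.93. That value is only (1 − 0.10)/(1 − 0.03): patients who died stay in the denominator for the whole year but cannot contribute an event. The plan derives event rates by Kaplan-Meier. If in-hospital deaths are early and those patients then leave the risk set, the rate is about 1 − (1 − d × a_D × c)(1 − a_S):
- c = 1, a_D = 10%: 1 − 0.990 × 0.98 = 2.98% against 1 − 0.997 × 0.98 = 2.29%; ratio 1.30.
- c = 0.5, a_D = 10%: 1 − 0.995 × 0.98 = 2.49% against 1 − 0.9985 × 0.98 = 2.15%; ratio 1.16.
- c = 0: 2% against 2%; ratio 1.00.

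Under the planned method the estimate moves towards the null and stops there.

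**The case against.** The strongest reply has four parts.

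*The detail may sit elsewhere.* The electronic case report form (S2 File) and the committee's procedures are not shown and may settle which document serves for a patient who dies and how ventricular fibrillation is coded. This is fair for detail that the article leaves out. Here, however, the article itself states a necessary condition and a closed list, and nothing in it opens either.

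*Loss in patients who die is not shown.* Hospitals may issue a death summary that the committee treats as the discharge letter. This stands: the loss is possible, not demonstrated. It is also a reason to say so in one sentence.

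*The list restricts only the serious category.* Ventricular fibrillation could still be counted as a cardiac arrhythmia. That is true only if the unqualified term is the outcome, and the Abstract names the serious one.

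*Independent adjudication is compatible with fixed criteria.* This stands. Committees apply preset criteria, and the rule does not contradict the statement that events are adjudicated independently.

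A reader might also extend the point to heart failure, because "Heart failure hospitalization must be documented in the diagnosis of the hospitalization discharge letter". The text does not support that. The endpoint is a hospitalization, and a discharge diagnosis is an ordinary source for it. Nor is it an error to leave out arrhythmias treated in an emergency department without admission. That choice trades sensitivity for specificity.

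**Conclusion.** The point holds for the secondary arrhythmia outcome. The definition as written leaves out some of the most severe arrhythmias, the source rule is silent on patients who die in hospital, and the outcome has more than one name. The first and third are plain on the text. Bias in the group comparison is conditional: it needs in-hospital deaths to differ between groups and capture in patients who die to be incomplete. If both hold and deaths are more frequent in the positive group, an excess of arrhythmia in that group would be attenuated. The size cannot be computed from the article; the ratios above rest wholly on assumed rates.

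Two stronger readings are tempting and not supported. One is that fatal events are lost to the study. Fatal cardiovascular events count in the primary outcome, which has no discharge-letter rule, and Table 2 records in-hospital deaths and arrhythmias. The other is that the comparison could be reversed. A ratio below 1 in the illustration needs zero capture in patients who die and also keeps them at risk after death. With Kaplan-Meier rates and early deaths leaving the risk set, the ratio is near 1.0.

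**What to change.** Make three changes to the article's definitions:

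1. Add ventricular fibrillation and cardiac arrest to the serious-arrhythmia list.
2. State that, for patients who die in hospital, a death summary or other source records reviewed by the committee suffice in place of the discharge letter.
3. Use serious cardiac arrhythmias as the name of the outcome in the Abstract, Table 2, and Outcomes and definitions.

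The text change is a few sentences and relies on records that the study already draws on. The cost is some extra record review for patients who died. The Monitoring section describes adjudication in the past tense. If it was already complete, the committee would have to look again at the arrhythmias affected by the new list and at patients who died in hospital.

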### Statistical analysis plan

We did not estimate a precise sample size, due to lack of literature reports and we aim to get the maximum numbers of patients possible.

Continuous variables will be presented as mean ± standard deviation. Categorical variables will be reported as absolute number and percentage. Differences in proportions will be tested with Chi-square test or Fishers exact test and differences in continuous variables will be tested with a Student’s t-test. Kaplan-Meier method will be used to derive the event rates at follow-up and to plot time-to-event curves. Patients not eligible for 1-year follow-up will be considered at risk until the date of last contact, at which point they will be censored.

To determine the predictors of cardiovascular death, a Cox proportional hazards model will be used together with the Wald test to compare the results between the groups (patients with positive vs. negative RT-PCR for SARS-CoV-2).

All p-values will be two-sided and a value <0.05 will be considered statistically significant. All data will be processed using the Statistical Package for Social Sciences, version 22 (SPSS Inc., Chicago, IL, USA).

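### Kaplan-Meier is fixed for 1-year rates of outcomes that death can preclude; with other deaths censored, as is standard, the rates overstate 1-year incidence

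*Protocol article*

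**What the plan says.** Under Outcomes and definitions, the protocol article gives the primary outcome as "Cardiovascular mortality at 1-year follow-up, defined according to the Academic Research Consortium-2". The secondary outcomes are myocardial infarction, stroke, heart failure hospitalization, pulmonary embolism, cardiac arrhythmias and major bleeding. They are not restricted to non-fatal events.

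For estimation, the Statistical analysis plan states that the "Kaplan-Meier method will be used to derive the event rates at follow-up and to plot time-to-event curves". Its only censoring rule is: "Patients not eligible for 1-year follow-up will be considered at risk until the date of last contact, at which point they will be censored". For the group contrast, "a Cox proportional hazards model will be used together with the Wald test to compare the results between the groups", that is, RT-PCR positive against negative.

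Table 2 (Data capture) lists among the data to be collected up to 1 year: "All cause death • Cardiovascular death • ACS • Stroke • Heart failure hospitalization". All-cause death therefore appears there under the Outcomes label, but it is not in the list under Outcomes and definitions. The article nowhere mentions competing risks, cumulative incidence functions or the handling of deaths from other causes.

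**The concern.** A patient who dies of a non-cardiovascular cause cannot later die of a cardiovascular one, and a patient who dies of any cause cannot later be admitted with heart failure. If such deaths are censored, Kaplan-Meier assumes that the dead would have gone on to have the event at the same rate as those still alive. One minus Kaplan-Meier then describes a hypothetical population in which other deaths do not occur, not the proportion of enrolled patients who have the event within a year. The second quantity is what a 1-year cardiovascular mortality means.

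The registry's product is a set of 1-year rates in two groups. An upward bias would affect the primary rate and every secondary rate. It would also distort the difference between the groups if mortality from other causes differs between them.

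This is not a detail left to a fuller plan. The article names the estimator, and an analysis plan that followed the sentence would carry the problem forward.

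**Working it through.** **Inputs.** From the article: a cause-specific primary outcome, 1-year follow-up, Kaplan-Meier for rates, Cox with a Wald test for the contrast. The article gives no death rate, event count or sample size, so there is no figure of its own to reproduce. All risks below are assumptions.

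**Constant hazards.** Let c be the true 1-year incidence of cardiovascular death (the Aalen-Johansen target) and d that of non-cardiovascular death.

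- Total hazard over the year: H = −ln(1 − c − d)
- Cardiovascular part: h = H × c/(c + d)
- One minus Kaplan-Meier with other deaths censored: 1 − exp(−h)

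Example, c = 2%, d = 20%: H = −ln(0.78) = 0.2485; h = 0.2485 × 2/22 = 0.02259; 1 − exp(−0.02259) = 2.23%, a relative excess of 11.7%.

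| Non-CV death d | 1 − KM when c = 2% | Relative excess |
|---|---|---|
| 2% | 2.02% | 1.0% |
| 5% | 2.05% | 2.6% |
| 10% | 2.11% | 5.4% |
| 15% | 2.17% | 8.4% |
| 20% | 2.23% | 11.7% |
| 30% | 2.38% | 19.1% |

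The relative excess is nearly the same for c from 1% to 5%. In absolute terms, for c of 1–5% and d of 1–20%, it runs from about 0.01 to 0.6 percentage points. A simulation of 400,000 patients with c = 2% and d = 20% gave 2.26% by one minus Kaplan-Meier against an observed incidence of 2.02%, in line with the formula.

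**Early deaths.** Apply the same formula in two successive periods and add the cardiovascular hazards. Put 90% of non-cardiovascular deaths in the first period and 20%, 50% or 80% of cardiovascular deaths there. With c = 2%, the relative excess is 2.9–4.5% at d = 5%, 6.0–9.4% at d = 10% and 13.0–20.9% at d = 20%.

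**Extreme case.** If every event follows all the competing deaths, and a proportion D has died by then, an incidence p among survivors gives a true incidence of (1 − D) × p, while one minus Kaplan-Meier gives p. The ratio is 1/(1 − D): 1.05 at D = 5%, 1.25 at 20%, 1.43 at 30%.

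**Group contrast.** Equal true cardiovascular death incidence of 2% in both groups, constant hazards:

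| d, positive vs negative | 1 − KM | Difference (points) | Ratio |
|---|---|---|---|
| 20% vs 2% | 2.23% vs 2.02% | +0.21 | 1.105 |
| 10% vs 2% | 2.11% vs 2.02% | +0.09 | 1.043 |
| 5% vs 5% | 2.05% vs 2.05% | 0 | 1.000 |
| 5% vs 10% | 2.05% vs 2.11% | −0.06 | 0.973 |

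The true difference is zero in every row.

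**The case against.** Several stronger readings are tempting, and the documents do not support them.

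- *The plan censors non-cardiovascular deaths.* It does not say so. Its one censoring rule concerns patients without a full year of follow-up. Censoring at death is what standard Kaplan-Meier implies, so it is an inference, though the natural one. If the deceased were instead kept in the risk set to 1 year, the overstatement would not arise, but nothing in the article suggests this.
- *The bias falls mostly on the COVID-positive group.* No mortality is given for either group, terminal disease is excluded in both, and the Discussion says that patients of any severity are included. Higher non-cardiovascular mortality among positives is plausible but remains a condition. The last two contrast rows show the distortion vanishing or reversing.
- *The primary comparison is biased.* The named contrast is Cox with a Wald test. With other deaths censored, this is a valid comparison of cause-specific hazards. It does not translate directly into a difference in 1-year risk, because that risk also depends on the hazard of the competing death.
- *The overstatement is 25–43%.* That needs early mortality of 20–30% and every event to follow it. Table 2 records acute coronary syndrome, stroke, embolism and arrhythmias in hospital as well, so not all events come late.

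It can also be said that a condensed article need not spell out the handling of intercurrent death. That excuses silence, but here the article names an estimator and gives no competing-risk provision with it.

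**Conclusion.** The point holds for the absolute rates, the curves and any absolute difference read from them. It does not extend to the hazard ratio or its test. The direction is certain once other deaths are censored: one minus Kaplan-Meier is at or above the true incidence, and strictly above it when other deaths precede later events.

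The size cannot be determined from the documents. With an assumed 2% cardiovascular death incidence, it runs from about 1% relative when non-cardiovascular mortality is 2% to about 12% when it is 20%, and to about 21% at 20% if most of those deaths are early. The 25–43% figures are an upper extreme. A bias that differs between groups follows only if their competing mortality differs.

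This should be fixed before analysis. It does not undermine the planned test.

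**What to change.** Replace the Kaplan-Meier sentence with text to this effect:

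*One-year rates and curves for cardiovascular death and for each secondary outcome will be estimated by group with the Aalen-Johansen cumulative incidence function. Non-cardiovascular death is the competing event for the primary outcome. For each secondary outcome, the competing event is any death that is not itself part of that event. The Cox model is a cause-specific hazard model, with competing deaths censored. All-cause death will be estimated by Kaplan-Meier and reported alongside.*

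Reporting non-cardiovascular death by group as well would let readers see whether the competing risk differs.

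The cost is a little more programming and possibly software beyond the SPSS version 22 named in the plan. Table 2 already collects all-cause and cardiovascular death to 1 year, so non-cardiovascular death can be identified. Dates of death are not listed in Table 2 and the case report form (S2 File) is not shown, so their availability should be confirmed; the planned Kaplan-Meier and Cox analyses need event and last-contact dates in any case.
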